#### Exercise: 15 Minutes

Individuals randomized to both groups will receive exercise designed to improve performance of both the deep neck flexor musculature as well as the scapular musculature. The physical examination will guide exercise interventions. See the exercise intervention treatment algorithm in Table 3 [61]. Exercise will be performed after manual therapy and before dry needling. The goal of this program is to increase endurance and control of the muscles in the cervicothoracic region. The exercise portion will also include a stretching program targeting the cervicothoracic muscles, which have been placed in a shortened position as a result of poor postures. Patients will be instructed to perform the exercises as a home program twice daily. Each patient will be provided with a home exercise log that includes pictures as well as descriptions of all exercises. This exercise log will be used to encourage patient compliance.

The patient will be instructed to maintain usual activity levels within the limits of pain. Advice to maintain usual activity has been found to assist in recovery from neck pain. Patients will be instructed to do all activities that do not increase symptoms and to avoid activities that aggravate symptoms.

#### Physical Examination Techniques That Will Guide Exercise Intervention

##### Neck Flexor Endurance

Endurance of the neck flexors will be assessed with the patient lying supine in a hook-lying position. The patient will retract the chin and lift the head and neck until the head is approximately one inch above the plinth. Once in position, a line will be drawn across one of the skin folds along the patient’s neck while the therapist maintains support just under the patient’s occiput. When either the line edges begin to separate or if the patient’s head touches the therapist’s hand for more than one second, the test will be terminated. This technique has been demonstrated to have moderate reliability (ICC of .67) [62].

##### Muscle Length Assessment

Length of the upper trapezius, latissimus dorsi, pectoralis minor, pectoralis major, levator scapulae, anterior and middle scalenes, and the suboccipital muscles will be assessed according to the descriptions provided by Cleland et al [60]. Percent agreement between examiners in our previous work ranged from 77% to 85% [63].

##### Muscle Strength Assessment

Strength of the upper quadrant will be tested according to the techniques described by Kendall [64]. Percent agreement between examiners in our previous work ranged from 81% to 91% [63].

#### Dry Needling: 15 Minutes

Individuals randomized to the MTEX-Needle group will receive dry needling targeting the posterior musculature of the cervical and thoracic spine. Dry needling will occur after the manual therapy and exercise at each treatment session. The physical examination findings will guide clinicians to allow them to determine which specific muscles will be targeted (see Table 4). Examples of posterior muscles that can be treated include the trapezius, levator scapulae, splenius capitis, semispinalis, spinalis capitis, multifidi, and suboccipital muscles. The therapist will needle at least six sites up to a maximum of 10 based on identification of MTrPs. If six sites failed to be identified, the therapist will address as many sites that are present and document the number of sites treated. Once the needle has been inserted manually into the trigger point, the needle will be pistoned in an up-and-down fashion so that 2- to 3-mm vertical motions occur (ie, fast-in and fast-out technique as described by Hong) at approximately 1 Hz for 25-30 seconds, with the aim of eliciting local twitch responses [65]. The maximum number of sessions of dry needling each participant will receive is six sessions, but therapists are instructed that if the patient has complete resolution of trigger points they do not need to continue with dry needling in subsequent sessions. The therapist also may discharge a patient at the therapist’s and patient’s discretion, as would normally be done in clinical practice.

#### Physical Examination That Will Guide Dry Needling Intervention: Trigger Point Assessment

The neck and upper quarter will be examined for the presence of the following: a hypersensitive spot in a palpable taut band, palpable or visible local twitch on pincer palpation, and reproduction of referred pain elicited by palpation of the sensitive spot. These criteria have been shown to exhibit good interexaminer reliability (κ=.84-.88) when applied by an experienced clinician [66].

#### Sham Dry Needling: 15 Minutes

Park Sham acupuncture needles (AcuPrime) will be used to perform sham dry needling in all patients randomized to the MTEX-Sham group. These needles have been reported to be indistinguishable from real needles in a patient who has not experienced dry needling before [67]. The device consists of two plastic tubes that slide into one another and allow the blunted needle to cause a pricking sensation when pushed against the skin. This sham needle allows the patient to have the feeling that the needle is entering the skin while also maintaining therapist-patient contact time and treatment explanation. Sham dry needling is proposed to have less effect when compared to true dry needling [68]. Sham dry needling sites will be determined in the exact same fashion as in the MTEX-Needle group by the physical therapist after assessment. Therapists will be asked to sham needle at least six sites up to a maximum of 10, but the muscles that are (sham) treated will be left at the discretion of the physical therapist. The number of sites and specific muscles (sham) treated will be recorded by the therapist. Only posterior muscles of the cervical spine and upper thoracic spine, the same muscles targeted in the dry needling group, will be treated in order to ensure patients will be blinded to whether they received the real or sham needling.

### Data Analysis

Descriptive statistics, including frequency counts for categorical variables and measures of central tendency and dispersion for continuous variables, will be calculated to summarize the data. Baseline demographic data will be compared across treatment groups to assess the adequacy of the randomization.

**Table 4 table4:** Dry needling intervention algorithm for treatment selection.

Assessment	Treatment
Trigger point assessment performed on the trapezius	Patient in prone, therapist identifies the hypersensitive spot in the trapezius
	The overlying skin will be cleansed with alcohol
	Once the needle has been inserted manually into the trigger point, the needle will be pistoned in an up-and-down fashion so that 2- to 3-mm vertical motions occur (ie, fast-in and fast-out technique as described by Hong) at approximately 1 Hz for 25-30 seconds, with the aim of eliciting local twitch responses
	After needle is removed, pressure with a cotton ball will be maintained to prevent excessive bleeding
	The number of sites and specific muscles treated will be recorded by the therapist
Trigger point assessment performed on the levator scapulae	Patient in prone, therapist identifies the hypersensitive spot in the levator scapulae
	The overlying skin will be cleansed with alcohol
	Once the needle has been inserted manually into the trigger point, the needle will be pistoned in an up-and-down fashion so that 2- to 3-mm vertical motions occur (ie, fast-in and fast-out technique as described by Hong) at approximately 1 Hz for 25-30 seconds, with the aim of eliciting local twitch responses
	After needle is removed, pressure with a cotton ball will be maintained to prevent excessive bleeding
	The number of sites and specific muscles treated will be recorded by the therapist
Trigger point assessment performed on the splenius capitis, semispinalis, spinalis capitis, and multifidi	Patient in prone, therapist identifies the hypersensitive spot in the splenius capitis, semispinalis, spinalis capitis, or multifidi
	The overlying skin will be cleansed with alcohol
	Once the needle has been inserted manually into the trigger point, the needle will be pistoned in an up-and-down fashion so that 2- to 3-mm vertical motions occur (ie, fast-in and fast-out technique as described by Hong) at approximately 1 Hz for 25-30 seconds, with the aim of eliciting local twitch responses
	After needle is removed, pressure with a cotton ball will be maintained to prevent excessive bleeding
	The number of sites and specific muscles treated will be recorded by the therapist
Trigger point assessment performed on the suboccipital muscles	Patient in prone, therapist identifies the hypersensitive spot in the suboccipital muscles
	The overlying skin will be cleansed with alcohol
	Once the needle has been inserted manually into the trigger point, the needle will be pistoned in an up-and-down fashion so that 2- to 3-mm vertical motions occur (ie, fast-in and fast-out technique as described by Hong) at approximately 1 Hz for 25-30 seconds, with the aim of eliciting local twitch responses
	After needle is removed, pressure with a cotton ball will be maintained to prevent excessive bleeding
	The number of sites and specific muscles treated will be recorded by the therapist

We will compare baseline variables between groups by using independent *t* tests or Mann-Whitney U tests for continuous data and chi-square tests of independence for categorical data. An intention-to-treat analysis will be utilized, in which all participants will be analyzed in the group to which they were originally assigned. All dropouts and the reasons for dropping out of the study will be reported. An a priori alpha level of .05 will be used for all analyses. All data will be checked to ensure they meet the assumptions for the inferential statistical analyses described below. If they do not meet the necessary assumptions, appropriate nonparametric procedures will be utilized. We will examine the primary aim with a two-way repeated-measures analysis of variance with treatment group (ie, manual therapy, exercise, and dry needling vs manual therapy, exercise, and sham dry needling) as the between-subjects independent variables and time (ie, baseline, 4 weeks, 6 months, and 12 months) as the within-subjects independent variable. The hypothesis of interest is the two-way group × time interaction. Bonferroni-corrected post hoc tests will be used to determine difference between group means.

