If a patient is determined to have met inclusion/exclusion criteria, they will be asked if they would like to participate in the study. If they choose to provide informed consent, each patient will complete the baseline questionnaires as well as the baseline outcome assessments. Demographic information will be collected for descriptive purposes, including age, gender, employment status, past medical history, mechanism of injury, location and nature of the patient’s symptoms, number of days since onset, number of previous episodes of neck pain, and treatment for previous episodes. Once patients are admitted to the study, no patient will be removed from the study for noncompliance and an intention-to-treat analysis will be used.

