## Discussion

### Principle Findings

Neck pain is commonly unresponsive or does not fully resolve with current treatment strategies, with 37% of patients going on to experience chronic neck pain of greater than one year [2]. Dry needling may be one intervention that could lead to improved outcomes when used in conjunction with exercise and manual therapy [11,39]. Anecdotally, in the clinical setting, a patient’s pain level commonly limits their ability to participate in active exercise interventions. As dry needling appears to have a significant treatment effect on reducing pain and increasing pressure pain threshold [38], it may facilitate a patient’s ability to perform a prescribed exercise program. In addition, it may improve patient compliance with exercise, which may lead to improved results from an exercise program.

Therefore, the aim of this trial is to determine if the addition of dry needling to an exercise and manual therapy treatment program will further reduce pain and improve disability in patients with mechanical neck pain, as compared to exercise and manual therapy and sham needling.

We hypothesize that patients who receive dry needling, manual therapy, and exercise will achieve greater reductions in pain and disability in the short term (ie, 4 weeks) and long term (ie, 6 and 12 months) compared to those who receive sham dry needling, manual therapy, and exercise.

As the use of dry needling by physical therapists becomes more widespread, and more therapists are trained in this approach, research is needed to support or refute its effectiveness. The results of this trial will assist in providing long-term outcomes examining the effectiveness of dry needling, which are currently lacking in the literature.

We anticipate the potential challenges to this study to include the following: difficulty with patient recruitment, patient compliance with follow-up schedule, and patients lost to follow-up over the 1-year, long-term, follow-up period. To address these challenges, we have utilized two large clinics in different locations in the United States to improve the ability to recruit patients in a timely manner. Further, we will provide a small financial reimbursement for patients as incentive for completion of the 4-week, 6-month, and 12-month follow-up in order to assist with compliance and reduce the numbers lost to follow-up.

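### The primary repeated-measures ANOVA, in its standard form, uses only patients with all four NDI scores, which does not fit the stated intention-to-treat analysis of all participants

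*Protocol article*

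**What the plan says.** All statements below are from the protocol article.

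- **Analysis set.** Data Analysis: "An intention-to-treat analysis will be utilized, in which all participants will be analyzed in the group to which they were originally assigned". The Subjects section makes the same commitment: "no patient will be removed from the study for noncompliance and an intention-to-treat analysis will be used".
- **Primary method.** Data Analysis: "We will examine the primary aim with a two-way repeated-measures analysis of variance with treatment group" as the between-subjects factor and "time (ie, baseline, 4 weeks, 6 months, and 12 months) as the within-subjects independent variable". The test that decides the primary aim is also fixed: "The hypothesis of interest is the two-way group × time interaction".
- **Missing outcomes.** Data Analysis says only: "All dropouts and the reasons for dropping out of the study will be reported". It names neither imputation nor a likelihood-based method, and it does not say that incomplete patients are excluded.
- **Expected losses.** Under Principle Findings, the anticipated challenges include "patients lost to follow-up over the 1-year, long-term, follow-up period". No rate is given. The 6- and 12-month assessments are mailed (end of the outcome measures section).
- **Sample size.** Power Analysis requires 29 per group for a 12-point NDI difference with SD 16, two-tailed alpha .05, and enrols 76. The surplus is said to cover dropouts before the 4-week follow-up.

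**The concern.** A classical repeated-measures ANOVA needs a complete row for each patient. Someone with baseline and 4-week NDI scores who does not return the 12-month questionnaire leaves the whole group-by-time test, and the observed 4-week score goes too. Unless values are imputed first, the population analysed is the completers, not everyone randomised.

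Two things would be at stake. A result presented as intention-to-treat would rest on a subset defined after randomisation, and it could be biased if the reasons for loss differ between arms. Patients who supplied usable data would also be discarded, at some cost in power. The dropout allowance looks only as far as week 4, whereas the primary test needs data to month 12.

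**Working it through.** **1. The plan's own figure.** Inputs from Power Analysis: difference 12, SD 16, two-sided alpha 0.05, so d = 12/16 = 0.75. The exact power of a two-sample t-test comes from the noncentral t distribution with 2n − 2 degrees of freedom and noncentrality 12/(16·√(2/n)). At 28 per arm it is 78.7% and at 29 per arm 80.1%, so 29 is reproduced. At 38 per arm (76/2) it is 89.7%. The surplus is 76 − 58 = 18 patients, or 18/76 = 23.7%.

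**2. Does the method need complete rows?** A standard repeated-measures ANOVA routine was given data with one cell missing. It refused to fit, reporting that the data were unbalanced.

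**3. Patients left.** The article gives no loss rate, so the following is an assumption: 5% missing at 4 weeks, 15% at 6 months, 25% at 12 months.

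- Nested (those missing early stay missing): 76 × 0.75 = 57, about 28 per arm.
- Independent misses: 76 × 0.95 × 0.85 × 0.75 = 46, or 23 per arm.

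Other assumptions give this range:

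| Assumed loss | Complete of 76 |
|---|---|
| Dropout by 12 months of 10% / 20% / 30% | 68 / 60 / 52 |
| Independent 5% / 10% / 15% / 20% at each follow-up | 65 / 55 / 47 / 39 |

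**4. Power for the plan's two-group contrast (12 points, SD 16, alpha 0.05).**

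| Complete per arm | Power |
|---|---|
| 38 (no loss) | 89.7% |
| 28 (nested) | 78.7% |
| 23 (independent) | 70.1% |

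This is the comparison on which the trial was sized, not the interaction test.

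**5. Bias among completers.** An adverse scenario is assumed: no true effect; SD 16 at every visit; correlation 0.6 between every pair of visits; 25% loss in each arm, linked to the 4-week score with odds ratio 2 per SD, in opposite directions in the two arms.

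- The mean 4-week score of those who stay shifts by 0.159 SD, down in one arm and up in the other. The false difference in 4-week means is 2 × 0.159 × 16 = 5.1 points.
- The other visits shift only through the correlation: 0.6 × 5.1 = 3.1 points at 12 months, and also 3.1 points at baseline, because the same patients are missing from every visit.
- The group-by-time interaction concerns change over time. The false difference in change from baseline is 5.1 − 3.1 = 2.0 points at 4 weeks and 3.1 − 3.1 = 0 at 12 months.
- For odds ratios 1.5 to 3, the 4-week figure runs from 1.3 to 2.9 points. The 12-month figure stays at 0, which depends on the equal correlations.

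**The case against.** The strongest reply is that the article nowhere prescribes deletion of incomplete patients. Imputing missing NDI scores before the ANOVA would keep all 76, and the imputation method is the kind of detail an article may leave to a fuller document. The intention-to-treat sentence can also be read mainly as a rule about allocation. This stands in part: a reader might infer that the promised analysis cannot be delivered, and the text does not support that. But the point is more than an absent detail. The article states both the analysis set and the primary method, and the two do not fit once a patient misses a visit.

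Other stronger readings also fail:

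- **Bias of 5 and 3 points.** A reader might take these group-mean differences at 4 weeks and 12 months as the bias in the primary test. They apply only to unadjusted post hoc comparisons of means and sit beside a 3-point baseline shift. The scenario is also extreme for a trial that blinds patients and assessors. With the same loss mechanism in both arms, the bias in the 12-month difference is at most about 1 point.
- **Power of 53%.** At 23 per arm, a t-test at alpha 0.05/3 has 52.7% power. Much of that drop is the Bonferroni correction: with all 38 per arm the same test has only 79%. If a change score is used, with the assumed correlation of 0.6, its SD is 16 × √(2 × 0.4) = 14.3 and power at 23 per arm and alpha 0.05 is 79%.
- **Sphericity and the fallback.** The uneven visit spacing and the clause "If they do not meet the necessary assumptions, appropriate nonparametric procedures will be utilized" might suggest that the primary hypothesis could change after the data are seen. The article fixes that hypothesis and says assumptions will be checked. The choice of correction or procedure is analysis-plan detail.

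The article also acts against loss: patients are reimbursed for completing each follow-up, and mailing is meant to raise the return rate.

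**Conclusion.** The point holds in a limited form. As worded, the intention-to-treat statement and the named primary method are not reconciled, and without an imputation step the primary result would probably be a completers analysis that also discards observed 4-week scores.

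The main harm is to the analysis population and the risk of bias. Power suffers only at higher loss: it stays at about 80% until roughly 18 of 76 patients are incomplete, is about 79% under the nested assumption and 70% under independent misses. The bias in change from baseline is about 2 points at 4 weeks and about 0 at 12 months, even under an adverse mechanism. All these sizes rest on assumed loss rates, correlation and dropout mechanism, since the article gives none of them. The stated sample size is not in error on this point. The wording should be fixed, but the design is not invalidated.

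**What to change.** In Data Analysis, replace the two-way repeated-measures ANOVA with a linear mixed model for repeated measures. Fit it to all observed NDI scores of all randomised patients, with group, time and group-by-time as fixed effects. Keep the interaction as the hypothesis of interest and take the Bonferroni-corrected contrasts at the follow-up times from this model. A patient with a 4-week score and no 12-month score then still contributes.

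If the ANOVA is to be kept, prespecified multiple imputation of missing NDI scores before it would also reconcile the text.

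The cost is a change of wording and slightly more analysis work, with no extra patients, visits or data. The mixed model relies on missingness at random given the observed scores, and the text should say so.

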**Objective:**

The aim of this trial will be to examine the short- and long-term effectiveness of dry needling delivered by a physical therapist on pain, disability, and patient-perceived improvements in patients with mechanical neck pain.

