The majority of existing studies lack adequate sample sizes, only collect short-term outcomes, frequently examine dry needling as a stand-alone intervention, and only treat one muscle for one to two sessions, which is not consistent with how dry needling is commonly performed clinically. Typically, clinicians will perform an examination to locate active and latent MTrPs and needle numerous active trigger points in a single session. They may then dry needle the patient over many sessions to achieve optimal effects. With the high prevalence of neck pain and its contribution to prolonged disability in patients, it is essential to identify optimal treatment approaches [1-3,5,6,40,41]. Therefore, the aim of this randomized clinical trial is to examine the long-term effects of a combination of manual therapy, exercises, and dry needling to the cervicothoracic region on pain and disability in individuals with acute or chronic mechanical neck pain resulting from postural dysfunction, trauma, or insidious onset who are referred to physical therapy.

We hypothesize that patients who receive dry needling, manual therapy, and exercise will achieve greater reductions in pain and disability in the short term (ie, 4 weeks) and long term (ie, 6 and 12 months) compared to those who receive sham dry needling, manual therapy, and exercise.

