### Power Analysis

Sample size and power calculations were performed using G*Power version 2 statistical software (Heinrich-Heine- Universität Düsseldorf) based on the minimal clinical improvement of 12 points on the NDI [51,69], assuming a standard deviation of 16 points, two-tailed, and an alpha level of .05. This requires a minimum sample size of 29 subjects per group. A total of 76 patients with a primary complaint of neck pain who meet the inclusion/exclusion criteria and consent to participate will be enrolled into the study. This sample size will yield greater than 80% power to detect both statistically significant and clinically meaningful changes in the NDI; additionally, this will control for dropouts prior to the 4-week follow-up.

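### The primary test is an omnibus group-by-time interaction with baseline NDI as an outcome level and no deciding visit, so it cannot by itself answer the directional, visit-specific hypotheses

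*Protocol article*

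**What the plan says.** Under Data Analysis, the protocol article states: "We will examine the primary aim with a two-way repeated-measures analysis of variance with treatment group" as the between-subjects factor and "time (ie, baseline, 4 weeks, 6 months, and 12 months) as the within-subjects independent variable". It continues: "The hypothesis of interest is the two-way group × time interaction". The next sentence adds: "Bonferroni-corrected post hoc tests will be used to determine difference between group means". It does not say which contrasts these are, how many there are, or whether the means are adjusted for baseline.

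The hypothesis in the Introduction, repeated in the Discussion, is directional and tied to visits: "greater reductions in pain and disability in the short term (ie, 4 weeks) and long term (ie, 6 and 12 months"). The Outcome Measures section makes the NDI the primary outcome and attaches no visit to it. Table 1 shows the NDI collected at baseline and at all three follow-ups.

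The Power Analysis takes a 12-point difference, SD 16, two-tailed alpha .05 and a minimum of 29 per group, with 76 patients to be enrolled. It names no visit for the calculation. Four weeks appears only in the remark on dropout: "this will control for dropouts prior to the 4-week follow-up".

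**The concern.** Two features of the stated test matter.

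First, the interaction has (2 − 1)(4 − 1) = 3 degrees of freedom and is non-directional. A significant result says that the two four-point profiles are not parallel. It does not say which arm did better, or when. A null result does not say which visit failed. Since no visit is named as deciding, the visit that carries the conclusion could be chosen after the results are known.

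Second, baseline NDI enters as an outcome level and not as a covariate. Treatment cannot affect baseline, so a difference measured from baseline carries baseline noise that covariate adjustment would remove. If the post hoc tests compare raw group means, a chance baseline imbalance passes into the estimates in proportion to the correlation.

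At stake are a clear answer to the trial's own question and some power. The validity of the randomised comparison is not at stake.

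**Working it through.** **Inputs from the protocol article.** Difference 12 points, SD 16, two-sided alpha .05, minimum 29 per group, 76 enrolled with equal allocation (76/2 = 38 per arm), and four time levels including baseline.

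**Assumptions, because the document gives no value.** SD 16 is the SD of a raw NDI score. The correlation rho is the same between any two visits (compound symmetry) and is taken as 0.3, 0.5 and 0.7. Follow-up is complete.

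**1. The plan's own figure.** For a two-sample t test at one time point, the noncentrality is 12 / (16 × √(2/n)).
- n = 28: 2.81, power 0.787.
- n = 29: 2.86, power 0.801.
- n = 38: 3.27, power 0.897.

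So 29 per group reproduces exactly as a comparison of two means at one visit. The calculation states no correlation and no number of visits, both of which sizing for the interaction would need.

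**2. What the interaction can distinguish.** Under compound symmetry the noncentrality is λ = (n/2) × Σ(d_t − d̄)² / (16² × (1 − rho)), with 3 and 3(2n − 2) degrees of freedom. Here d_t is the between-arm difference at each time level.
- Lasting benefit (0, 12, 12, 12): mean 9, sum of squares 81 + 3 × 9 = 108.
- Benefit at 4 weeks only (0, 12, 0, 0): mean 3, sum of squares 81 + 3 × 9 = 108.
- Benefit at 12 months only (0, 0, 0, 12): 108.
- Lasting harm (0, −12, −12, −12): 108.

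At n = 38 and rho 0.5, λ = 19 × 108 / 128 = 16.03 and power is 0.93 for all four patterns. The test is equally likely to be significant under each.

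**3. Power of the alternatives at 38 per arm, 12 points.** The SD is 16√(2(1 − rho)) for a change score and 16√(1 − rho²) for the baseline-adjusted difference. The variance ratio of adjusted to change score is (1 + rho)/2 = 0.65, 0.75, 0.85.

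| Analysis | rho 0.3 | rho 0.5 | rho 0.7 |
|---|---|---|---|
| Interaction, constant effect (0, 12, 12, 12) | 0.81 | 0.93 | 0.995 |
| Interaction, fading effect (0, 12, 6, 0) | 0.78 | 0.91 | 0.99 |
| Change score, one visit | 0.78 | 0.90 | 0.99 |
| Baseline-adjusted difference, one visit | 0.92 | 0.96 | 0.995 |

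An unadjusted comparison at one visit has power 0.897 at alpha .05. With Bonferroni over three follow-ups (alpha .05/3) it has 0.79.

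**4. At the stated minimum of 29 per arm.** The interaction with a constant effect has 0.69/0.84/0.975. The adjusted single-visit difference has 0.84/0.90/0.98. The unadjusted comparison with Bonferroni over three has 0.65.

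**5. Chance imbalance.** The standard error of the baseline difference between arms at 38 per arm is 16 × √(2/38) = 3.67 NDI points.

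**The case against.** The strongest defence is that, with baseline as a time level, the interaction does test whether change differs between arms, which is close to the hypothesis of greater reductions. Post hoc tests then follow and can supply direction and visit. That stands. A reader might infer that the plan never tests its hypotheses, and the document does not support this. What remains is that the answer rests on post hoc contrasts while the named test of interest has neither direction nor visit.

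A reader might also infer that the baseline measurement is wasted. It is not: it enters through within-patient change, only less efficiently than as a covariate. Nor does the text establish that the post hoc tests ignore baseline. It states no adjustment, and does not say whether raw means or changes are compared.

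A third tempting reading is that sections contradict each other on the primary visit. The abstract's Objective is to "examine the short- and long-term effectiveness of dry needling". The Introduction says "the aim of this randomized clinical trial is to examine the long-term effects of a combination of manual therapy, exercises, and dry needling", but its hypothesis, stated directly afterwards, covers 4 weeks, 6 months and 12 months. The Power Analysis mentions 4 weeks only for dropout. These can be read together; the gap is that no visit is singled out.

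Finally, the power loss depends on a correlation that the document does not give, and at 0.7 it almost disappears. If SD 16 is instead the SD of change, the single-visit change score has power 0.897 at 38 per arm at every correlation, though the variance ratio (1 + rho)/2 still holds. An article may also leave contrast details to a fuller document. The choice of test, the baseline level and the hypothesis of interest are, however, stated here.

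**Conclusion.** The point holds in a limited form. The named primary test is non-directional and not tied to a visit, no visit decides success, and the sample size belongs to a different, single-visit test. This part follows from the text and from an exact reproduction of 29 per group; it does not depend on the assumed correlation.

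The efficiency part is an improvement and does not correct an invalid analysis. At 38 per arm, baseline adjustment at one visit gains about 11 percentage points of power over the constant-effect interaction at rho 0.3 (0.92 against 0.81), about 3 at rho 0.5 (0.96 against 0.93), and nothing visible at rho 0.7. With full enrolment and follow-up the interaction itself stays above 80% for a constant 12-point effect at these correlations, and falls to 0.78 only for the fading effect at rho 0.3. The unadjusted Bonferroni comparison, at 0.79 over three follow-ups, falls just short of the power above 80% that the Power Analysis claims. These figures assume compound symmetry, SD 16 as the raw-score SD and no loss to follow-up.

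**What to change.** Before any between-arm results are seen:

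- Name one primary NDI visit, or state a multiplicity rule across 4 weeks, 6 months and 12 months. The choice is the sponsor's.
- Make the primary result the between-arm NDI difference at that visit, adjusted for baseline NDI, with a 95% CI. Estimate it by ANCOVA, or by a longitudinal model in which only the follow-up visits are outcomes and baseline is a covariate.
- Tie the Power Analysis to that contrast, stating the visit, what SD 16 refers to, and any correlation assumed.
- Treat the remaining visits as secondary and the omnibus interaction as descriptive. Analyse the VAS in the same way.

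The cost is a change of wording. Baseline NDI and VAS are already collected from every patient, and no visit or patient is added. The one real commitment is to a primary visit or rule.
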